## Abstract

Microvascular injury is present in a large proportion of patients with ST-elevation myocardial infarction (STEMI) despite successful revascularization. Ticagrelor potentially mitigates this process by exerting additional adenosine-mediated effects. This study aims to determine whether ticagrelor is associated with a better microvascular function compared to prasugrel as maintenance therapy after STEMI. A total of 110 patients presenting with STEMI and additional intermediate stenosis in another coronary artery will be studied after successful percutaneous coronary intervention (PCI) of the infarct-related artery. Patients will be randomized to treatment with ticagrelor or prasugrel for 1 year. FFR-guided PCI of the non-infarct-related artery will be performed at 1 month. Microvascular function will be assessed by measurement of the index of microcirculatory resistance (IMR) in the infarct-related artery and non-infarct-related artery, immediately after primary PCI and after 1 month. The REDUCE-MVI study will establish whether ticagrelor as a maintenance therapy may improve microvascular function in patients after revascularized STEMI.

## Introduction

Percutaneous coronary intervention (PCI) in patients with ST-elevation myocardial infarction (STEMI) leads to an improved patency rate of the infarct-related artery, a lower incidence of heart failure, and ultimately an improved survival as compared to thrombolytic treatment [1]. However, problems that frequently occur after restoration of the epicardial blood flow are inadequate myocardial reperfusion and microvascular injury (MVI) [2].

MVI can be visualized by non-invasive methods using cardiovascular magnetic resonance imaging (CMR) or measured by invasive methods such as intracoronary thermodilution [3]. MVI as assessed by CMR is related to left ventricular remodeling and clinical outcome after STEMI [4, 5].

From the acute to late phase of a revascularized myocardial infarction, several mediators are thought to contribute to the development of MVI. These factors involve the appearance of intraluminal platelets, fibrin thrombi, and neutrophilic granulocytes, resulting in inflammatory cell plugging, formation of microthrombi, endothelial activation and injury, and finally MVI. Vasoconstriction follows as a result of endothelial dysfunction with decreased levels of nitric oxide and increased levels of endothelin-1. Furthermore, the imbalance in coagulation factors and influx of inflammatory cells can cause vascular leakage and hemorrhage [6, 7]. Adenosine, a substance naturally present in the blood, has an inhibitory effect on several of these processes [8, 9].

Currently, in patients with STEMI, the P2Y_12_-receptor antagonists ticagrelor and prasugrel, in addition to aspirin, are the recommended antiplatelet drugs according to European and American guidelines [10, 11]. The efficacy of ticagrelor and prasugrel in reducing platelet activity is comparable [12]. The long-term effects on clinical outcome are presently subject to investigation [13]. Interestingly, ticagrelor, besides its antiplatelet effects, increases adenosine concentration in the blood plasma by inhibition of intracellular reuptake and might therefore have an additional beneficial effect by preventing MVI [14–17]. Therefore, we designed a randomized study, comparing the effects of ticagrelor and prasugrel on MVI and endothelial dysfunction after STEMI.

## Methods

The Reducing Micro Vascular dysfunction In revascularized ST-elevation myocardial infarction patients by off-target properties of ticagrelor (REDUCE-MVI) study is a multicenter trial with a prospective, randomized, open-label, blinded-endpoint (PROBE) study design. Current participating centers are the VU University Medical Center (Amsterdam, the Netherlands), the Erasmus Medical Center (Rotterdam, the Netherlands), the Medisch Spectrum Twente (Enschede, the Netherlands), and the Hospital Clínico San Carlos (Madrid, Spain). A flow chart of the study design is shown in Fig. 1.

**Fig. 1 Fig1:**
[figure not shown]
Flow chart of the REDUCE-MVI study. *CMR* cardiovascular magnetic resonance, *IMR* index of microcirculatory resistance, *OCT* optical coherence tomography, *PCI* percutaneous coronary intervention, *RHI* reactive hyperemia index, *STEMI* ST-elevation myocardial infarction

## Patient Enrolment

On hospital arrival, patients presenting with an acute STEMI will be screened for participation in the study according to the inclusion and exclusion criteria (Table 1). ST-elevation criteria are used according to current ESC guidelines [10]. After successful PCI, witnessed oral informed consent will be obtained and documented, before proceeding with study measurements. After the procedure, written informed consent in native language will be obtained from all individual participants that will be included in the study. Hereafter, patients will be randomized to treatment with either ticagrelor or prasugrel. A total of 110 patients will be enrolled in the study.

**Table 1 Tab1:** Inclusion and exclusion criteria

Inclusion criteria	Exclusion criteria
Acute STEMI <12 h The patient has received a loading dose ticagrelor 180 mg before start of PCI Successful PCI of the infarct-related artery with a modern DES Intermediate stenosis in a non-infarct-related artery (50–90 %) Provision of informed consent	Age <18 or ≥75 Body weight <60 kg History of myocardial infarction, coronary artery bypass graft, stroke, or transient ischemic attack Congestive heart failure, left ventricle ejection fraction <35 % Severe liver or kidney dysfunction Bleeding diathesis, platelet count <100,000/mm^3^ Indication or use of (novel) oral anticoagulant therapy Cardiogenic shock Chronic total occlusion, left main disease Inability or contra-indication for MRI Inability to be followed on-site Limited life expectancy

*DES* drug-eluting stent, *MRI* magnetic resonance imaging, *PCI* percutaneous coronary intervention, *STEMI* ST-elevation myocardial infarction

## Coronary Angiography and Revascularization at Index and 1 Month

PCI will be performed according to standard procedures and is left to the discretion of the operator. All patients will receive a loading dose of heparin, aspirin, and the P2Y_12_ inhibitor ticagrelor in the ambulance before primary PCI with a third-generation drug-eluting stent (DES) (standard of care in participating centers). After successful primary PCI, myocardial tissue perfusion of the infarct-related area will be assessed by determining the myocardial blush grade [18].

After 1 month, patients will undergo clinically indicated FFR-guided PCI of the intermediate lesion in the non-infarct-related artery.

## Pharmacologic Treatment

Patients will be randomly assigned to use either ticagrelor 90 mg BID or prasugrel 10 mg SID as a maintenance therapy continued for 1 year according to current international guidelines [19]. Concomitant medical therapy will be left to the discretion of the treating physician.

## Endpoints

The primary objective of this study is to determine whether ticagrelor at treatment steady-state in revascularized STEMI patients is associated with an improved microvascular function as measured with IMR, compared to prasugrel. Both treatment groups are subjected to the same measurements at three time points. The function of the coronary microcirculation is considered as primary endpoint which will be assessed by determining the index of the microcirculatory resistance (IMR) [3]. Microcirculatory resistance measurements of the infarct-related artery and secondarily of the non-infarct-related artery will be performed directly after primary PCI and after 1 month. Secondary endpoints will be coronary endothelialization, left ventricular function, and infarct size at 1 month, as well as peripheral endothelial function and several biochemical markers of endothelial function, measured at baseline and at follow-up after 1 month and 1 year.

## Index of Microcirculatory Resistance

IMR in the infarct-related artery will be measured after 1 month and compared to IMR immediately after primary PCI. Secondly, IMR in the non-infarct-related artery will be determined after 1 month and compared to measurements at baseline (Fig. 2).

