## Sample Size Calculation

The study is powered using a superiority design with the null hypothesis that IMR will be significantly improved in the ticagrelor group in comparison to the prasugrel group. A difference of IMR means of 7 at 1 month follow-up between the two treatment groups, with a standard deviation of 12, is expected [26]. To be able to reject the null hypothesis that the means of both treatment groups are equal with a power of 80 % (with significance level *α* = 0.05), 47 subjects in each group are required. Assuming a loss of follow-up of maximally 15 %, it will be necessary to include a total of 110 patients in the study. After 50 % inclusion (*n* = 55) with complete 30-day follow-up, an interim analysis will be performed to verify the assumed standard deviation and, if necessary, we might adjust the total sample size needed to achieve an adequate power.

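### The primary IMR variable is not fixed: one section compares 1 month with post-PCI, the sample size uses 1-month means; one baseline-adjusted analysis would settle it

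*Protocol article*

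**What the plan says.** Three sections of the protocol article bear on the primary variable.

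- **Endpoints** makes coronary microvascular function, assessed by IMR, the primary endpoint and gives the measurement times: "Microcirculatory resistance measurements of the infarct-related artery and secondarily of the non-infarct-related artery will be performed directly after primary PCI and after 1 month". It does not say whether the outcome is the 1-month value or the change between the two times.
- **Index of Microcirculatory Resistance** states a comparison over time: "IMR in the infarct-related artery will be measured after 1 month and compared to IMR immediately after primary PCI". It then treats the non-infarct-related artery in the same way.
- **Sample Size Calculation** states a comparison between arms at one time: "A difference of IMR means of 7 at 1 month follow-up between the two treatment groups, with a standard deviation of 12, is expected". The hypothesis matches: "To be able to reject the null hypothesis that the means of both treatment groups are equal". It requires 47 per group for 80% power, and 110 in total after allowing for 15% loss. It also plans a check of the SD once 55 patients have complete 30-day follow-up, with a possible change of sample size.

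The only SD given is 12. There is no SD for the post-PCI IMR, no SD for the change, and no correlation between the two measurements.

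**The concern.** A 1-month value and a change from the post-PCI value are different outcome variables with different SDs. The primary variable belongs in the protocol, and here two sections point to different ones. Three things are at stake.

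- **Power.** The sample size was derived for one variable. It carries over to the other only if the two measurements are correlated strongly enough.
- **The interim SD check.** With the variable open, it is unclear which SD is to be compared with 12. Checking the 1-month SD and then analysing change could confirm a sample size that is too small for that analysis. Checking the SD of change and then analysing 1-month means could alter the sample size for no reason.
- **Choice of analysis.** The two analyses can give different p-values for the same hypothesis. Treatment is open-label, so the choice should be fixed in writing. Blinded core-laboratory calculation of IMR protects the measurement, but not the choice of analysis.

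**Working it through.** **Inputs from Sample Size Calculation:** difference 7, SD 12, α = 0.05, power 80%, 47 per group. The article does not state whether the test is one- or two-sided. Two-sided gives 47 and one-sided gives 37, so the plan is two-sided.

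**Step 1: reproduce the plan.** For a difference in means,

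n per group = 2 × (1.96 + 0.842)² × 12² / 7² = 46.1, rounded up to 47.

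Power with 47 per group is 80.7% by the normal approximation and 79.9% by the noncentral t. For loss, 94 / 0.85 = 110.6, against 110 stated, which is close enough. The stated size is right for 1-month means.

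**Step 2: SD of a change score.** Let s0 be the post-PCI SD, s1 = 12 the 1-month SD and ρ their correlation. Then

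SD(change) = √(s1² + s0² − 2ρ·s0·s1).

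Randomisation makes the expected difference between arms the same for change as for the 1-month value, so 7 still applies. SD(change) equals 12 when s0² = 2ρ·s0·s1, that is, ρ = s0 / (2·s1). Below that value the change score has less power than planned; above it, more. The threshold is 0.5 for equal SDs, and 0.375, 0.625 and 0.75 for s0/s1 of 0.75, 1.25 and 1.5.

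**Step 3: SD after baseline adjustment.** For analysis of covariance (ANCOVA) the residual SD is 12 × √(1 − ρ²), whatever s0 is.

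**Step 4: power with 47 per group.** Noncentral t, difference 7. ρ is assumed throughout, and SDs are assumed equal for the change score, so SD(change) = 12 × √(2(1 − ρ)).

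| ρ (assumed) | SD of change | Power, change | ANCOVA SD | Power, ANCOVA |
|---|---|---|---|---|
| 0 | 16.97 | 50.8% | 12.00 | 79.9% |
| 0.2 | 15.18 | 60.0% | 11.76 | 81.5% |
| 0.3 | 14.20 | 65.7% | 11.45 | 83.5% |
| 0.4 | 13.15 | 72.4% | 11.00 | 86.3% |
| 0.5 | 12.00 | 79.9% | 10.39 | 89.8% |
| 0.6 | 10.73 | 87.9% | 9.60 | 93.8% |
| 0.7 | 9.30 | 95.1% | 8.57 | 97.5% |

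For scale, at ρ = 0.3 with equal SDs a change score needs 46.1 × 2 × 0.7 = 64.6, so 65 per group. That is 130 / 0.85 = 153 in total.

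**Step 5: why adjustment removes the ambiguity.** Write Y0 and Y1 for the two IMR values and T for treatment. The model Y1 − Y0 = a + bT + cY0 rearranges to Y1 = a + bT + (c + 1)Y0. The treatment effect b is the same either way. ANCOVA is also at least as precise as both alternatives. Its variance factor 1 − ρ² is no more than 1. With r = s0/s1, it falls short of the change-score factor 1 + r² − 2rρ by (r − ρ)², which cannot be negative.

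**Step 6: is the covariate valid?** Patient Enrolment puts oral consent before the study measurements, then written consent, then randomisation. The post-PCI IMR therefore precedes allocation and is already part of the schedule.

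**The case against.** The best defence is that the article does identify the comparison it powers. Sample Size Calculation is explicit about 1-month means and gives the matching null hypothesis, and the objective in Endpoints concerns ticagrelor against prasugrel at steady state. The IMR section describes measurement. It names no test and no contrast between arms for the change, and its wording would even fit a baseline-adjusted analysis. A reader might infer that the plan commits to a change-score test and is therefore underpowered. The documents do not support that: no section states such a test, and the shortfall appears only under an assumed correlation below the threshold. At 0.6 or 0.7 with equal SDs, a change score exceeds 80% power.

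A second defence is that covariate models are commonly left to the analysis plan, which is not shown. This stands. An unadjusted comparison of 1-month means is valid in a randomised trial, and not stating a covariate is no error in itself.

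A third is that the SD will be checked at the interim and that IMR is calculated blind. Both help in part, but the SD check works only once it is clear whose SD is meant.

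After these defences, the mismatch between the IMR section and Sample Size Calculation remains, and Endpoints does not resolve it.

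**Conclusion.** The point holds as an inconsistency that should be fixed; it is not a must-fix error. The sample size is correct for 1-month means. The consequence for power is conditional: if change were analysed, the stated 80% would hold only when the correlation reaches s0 / (2·s1). The range of roughly 51% to 95% for correlations from 0 to 0.7 rests on equal SDs at the two times. A more variable post-PCI IMR would raise the threshold and a less variable one would lower it. The documents give no figure that places this trial within that range, so they do not show an actual power deficit.

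**What to change.** Make four wording changes, in the protocol or the analysis plan:

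1. In Endpoints, name infarct-artery IMR at 1 month as the single primary variable, compared between arms by ANCOVA with the post-PCI, pre-randomisation IMR as covariate.
2. In Index of Microcirculatory Resistance, reword the comparison over time so that change within each arm is descriptive.
3. Analyse the non-infarct-related artery in the same way, as the secondary comparison.
4. In Sample Size Calculation, state that the interim check concerns the SD of this primary analysis.

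The cost is a few sentences, with no new measurements and no more patients. The planned 47 per group can stay, because adjustment does not lower power below the plan beyond the effect of one degree of freedom. A rule for patients with a missing post-PCI IMR is also needed.

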**Fig. 2 Fig2:**
[figure not shown]
Primary PCI procedure with subsequentmeasurement of the IMR. **a** Angiographic demonstration of the presence of a subtotal occlusion of the right coronary artery (RCA) in its mid portion and **b** final result after successful reopening of the RCA with subsequent implantation of two DES stents; **c** measurement of the IMR. The recording is obtained from a pressure wire in the mid of the right coronary artery of a patient after primary PCI. The *panel* is divided into two *windows*; the *upper window* displays the pressure segments recorded during each saline injection, separated from each other by *white vertical lines* (mean proximal arterial pressure (P_a_) = 91 and mean distal arterial pressure (P_d_) = 81 result into a fractional flow reserve (FFR) = 0.89). The lower graph displays saline injections at baseline (*blue*) and during hyperemia (*yellow*). Between the two graphs are mean transit time values at baseline (preceded by “Bas”), and during hyperemia (preceded by “Hyp”)

By using a coronary pressure and temperature-sensitive guidewire (Certus™, ST Jude Medical, Uppsala, Sweden) and modified software, the transit time of room-temperature saline injected in a coronary artery can be determined. After an intracoronary injection of 200 mcg nitroglycerine to establish epicardial coronary vasodilatation, the guidewire is calibrated outside the body, equalized with aortic pressure at the ostium of the guide catheter, and then advanced into the distal third of the artery and distal to the stent in the infarct-related artery. The mean transit time at baseline is obtained by administering three times 3 mL of intracoronary saline. Thereafter, hyperemia is induced by administering adenosine at 140 mcg/kg per minute intravenously and measurement of mean transit time is repeated. Aortic and distal coronary pressures are recorded simultaneously. The distal coronary pressure divided by the inverse of the hyperemic mean transit time then provides the IMR. This calculation will be performed by independent and blinded analysts in a core laboratory.

## Optical Coherence Tomography

Optical coherence tomography (OCT) will be performed at 1 month with a Dragonfly™ OCT catheter (St Jude Medical, St. Paul, MN, USA) using a motorized pullback device. OCT pullbacks will be performed at a speed of 20 mm/s in the infarct-related and non-infarct-related arteries, using in general a contrast flush rate of 3 mL/s in the right coronary artery and 4 mL/s in the left coronary artery. The occurrence of subclinical stent thrombus, stent malposition, and edge dissections will be assessed. All acquired images are sent to a core laboratory for blinded evaluation (endothelial aspects of the infarct- and non-infarct-related artery) using a standardized protocol.

## Peripheral Endothelial Function

The peripheral endothelial function will be measured within 24 h after primary PCI, at 1 month, and 1 year follow-up.

EndoPAT^®^ (Itamar Medical Ltd., Caesarea, Israel) is a validated device indicated for non-invasive endothelial and microvascular function assessment [20–22]. EndoPAT^®^ will be used to measure the finger arterial pulsatile volume changes that indicate changes in vascular tone, by modified plethysmographic probes placed on the index finger of each hand [23]. The measurements will be performed at rest in a convenient, low stimulus environment. Each recording consists of subsequently 5 min of baseline measurement, 5 min of occlusion time of the brachial artery by a blood pressure cuff, and 5 min post-occlusion measurement (hyperemic period). Measurements will be performed on the contralateral arm of the access site of angiography. The access site extremity is used as a reference to control for concurrent non-endothelial-dependent systemic changes in vascular tone.

The reactive hyperemia index (RHI) and its natural logarithm are then calculated as the ratio of the magnitude of the average post-occlusive pulse volume amplitude to the average pre-occlusive pulse volume amplitude, corrected for baseline vascular tone.

## Cardiovascular Magnetic Resonance

After 1 month and optionally at baseline (day 2–7), CMR will be performed with a 1.5 or 3.0 Tesla scanner using a phased array cardiac receiver coil. All images are ECG-gated and acquired during mild end-expiration breath-holding. Cine long- and short-axis slices are obtained to examine regional and global left ventricular function, volumes, and ejection fraction. Evaluation of myocardial ischemia will be assessed with first-pass perfusion imaging of a gadolinium-based contrast agent during the administration of 140 mcg/kg per minute of adenosine intravenously. Finally, late gadolinium-enhanced (LGE) images are acquired 10 min after perfusion imaging, to identify the size and extent of myocardial infarction and, in addition, the presence and extent of MVI. When performed at baseline, T2-weighted imaging will be acquired in short-axis planes for the detection of intramyocardial hemorrhage and infarct-related edema. All CMR analyses will be performed in a core laboratory by blinded observers using a standardized protocol.

## Blood Collection and Storage

Blood samples for laboratory testing will be drawn at baseline and at 1 month and 1 year follow-up according to standard procedures. The testing includes standard biochemistry and hematology tests (e.g., renal function tests, cardiac biomarkers, lipid profile, and blood cell counts). Furthermore, extra blood samples will be collected and stored at −80 °C. At the end of the study, all samples will be analyzed by the laboratory at the VU University Medical Center. The plasma levels of ticagrelor will be examined as well, and P2Y_12_ inhibition levels will be assessed by VerifyNow testing (Accumetrics, San Diego, CA, USA). The effect of ticagrelor on inflammatory markers and cells, such as cell adhesion molecules and monocytes, will be studied concomitantly. In addition, the level of biochemical markers for endothelial function, like asymmetrical dimethylarginine, will be measured, which allows linking these results to the microvascular function.

## Registration of Adverse Events

Adverse events (AEs) are evaluated and registered during index hospitalization and at 1 month and 1 year follow-up. AEs occurring in external participating centers will be reported to the sponsor. A serious adverse event (SAE) is a severe undesirable event in which there was no necessarily causality with the study. The relationship of SAEs to study treatment or procedures will be assessed by the investigators and communicated to AstraZeneca.

As a safety measure, bleeding complications will be monitored during the entire study period, categorized to the most recent criteria (Bleeding Academic Research Consortium, Thrombolysis in Myocardial Infarction [24], and Global Use of Strategies to Open Occluded Coronary Arteries [25]) and analyzed for both treatment groups.

Once a year, the sponsor will submit a safety report to the accredited medical ethics committee and competent authority. After 50 % inclusion, an interim analysis will be performed, with respect to safety endpoints, AEs, and SAEs. An independent data safety monitoring board, composed of experienced cardiologists and a statistician, will be responsible for reviewing patient safety and study integrity.

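### The article defines a serious adverse event by severity, with no outcome criterion, so some serious events would be labelled non-serious and miss the steps stated only for SAEs

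*Protocol article*

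**What the plan says.** Everything on this point stands in the protocol article, Methods, Registration of Adverse Events.

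- Definition: "A serious adverse event (SAE) is a severe undesirable event in which there was no necessarily causality with the study". No list of outcomes follows, there or elsewhere in the article.
- Step stated for SAEs only: "The relationship of SAEs to study treatment or procedures will be assessed by the investigators and communicated to AstraZeneca".
- General registration, with no severity threshold: "Adverse events (AEs) are evaluated and registered during index hospitalization and at 1 month and 1 year follow-up".
- Reporting from other centers, again for all AEs: "AEs occurring in external participating centers will be reported to the sponsor".
- Half-way review: "After 50 % inclusion, an interim analysis will be performed, with respect to safety endpoints, AEs, and SAEs".
- Bleeding: "bleeding complications will be monitored during the entire study period, categorized to the most recent criteria". Three sets of bleeding criteria are named, and the analysis covers both treatment groups.
- Annual report: "Once a year, the sponsor will submit a safety report to the accredited medical ethics committee and competent authority". The article does not say which events it contains.

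**The concern.** Severity and seriousness are different attributes of an adverse event. Severity grades intensity. Seriousness depends on what the event led to: death, threat to life, admission or a longer stay, persistent or significant disability, or another medically important outcome. The article's sentence puts the first in place of the second.

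The substitution causes errors in both directions. A moderate event that brings the patient back into hospital is serious but fails a severity test. An intense but short-lived event without consequence passes that test but is not serious.

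Two things are at stake. First, an event wrongly labelled non-serious gets neither the investigator's judgement of relatedness nor the communication to the company, because the text provides these only for SAEs. Second, SAEs are named as a category of their own at the half-way review, so the reviewers would see a category assembled by the wrong criterion.

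**Working it through.** No arithmetic decides this point, and the article gives no figure to reproduce. The check is to take one test event through each safety provision in Registration of Adverse Events. The test event is serious by outcome (it causes readmission) but moderate in intensity.

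| Provision | Depends on the SAE label? | What happens to the test event |
|---|---|---|
| SAE definition ("A serious adverse event (SAE) is a severe undesirable event in which there was no necessarily causality with the study") | It sets the label | Not severe, so classed as a non-serious AE |
| Registration at index stay, 1 month and 1 year | No; all AEs | Registered |
| Reporting from external centers to the sponsor | No; all AEs | Reported |
| Relatedness assessment and communication to the company | Yes; stated for SAEs | Neither is provided for |
| Half-way review | Partly; it covers safety endpoints, AEs and SAEs | Seen, but under the AE heading |
| Bleeding monitoring and analysis | No | If it is a bleed: captured, categorized and analyzed in both groups |
| Annual safety report | Not stated | Cannot be determined |

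The wrong label therefore matters in two rows. The relatedness assessment and communication to the company are lost, and the event appears in the wrong category at the half-way review. For a bleed, the same two consequences remain, but the event itself is not lost to the safety analysis.

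A sense of scale for the second consequence: 50% of the planned 110 patients is 0.50 × 110 = 55, the number that Sample Size Calculation also gives for the half-way point. Each patient whose only serious event is mislabelled lowers the observed proportion of patients with an SAE by 1/55 = 1.8 percentage points. An intense but non-serious event counted as an SAE moves the proportion the other way. The article contains nothing from which the number of such patients could be estimated, so no net effect can be given.

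**The case against.** The strongest defence is that this is a journal article condensing a fuller protocol. Itemised seriousness criteria belong in that fuller document, and their absence from the article is not an error. The sentence seems written mainly to say that SAEs are recorded whatever their cause. Its English is loose, and the article defines no scale of mild, moderate and severe, so the adjective may be only an informal gloss. Nor does the article show that sites classify events from this one sentence.

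Much of this is fair, and it limits the weight of the point. It does not remove it. The article does not leave the definition to another document; it states one, and its criterion is the wrong one. If the full protocol has the proper criteria, the article misreports them. If it does not, the error is operational.

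A reader might also infer three stronger consequences that the text does not support.

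- **That these events escape the half-way safety review.** The review expressly includes AEs and safety endpoints, so they are seen under a different label.
- **That they are left out of the annual safety report.** The content of that report is not stated and is not limited to SAEs, so exclusion cannot be shown.
- **That the bleeding comparison between the drugs is biased.** Bleeding is monitored throughout and categorized by named criteria regardless of SAE status. The trial is open-label, and a judgement of intensity is more open to influence than the fact of an admission. But bleeding is the only safety outcome for which this section states an analysis in both groups, and that analysis does not use the SAE label.

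**Conclusion.** The point holds in a limited form. The printed definition rests on severity, names no outcome, and would label some serious events as non-serious. The consequences that the text supports are the loss of the relatedness assessment and communication to the company for those events, and a misclassified SAE category at the half-way review.

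The weight is minor. Registration of AEs, bleeding monitoring and the primary IMR analysis are unaffected. The number of events involved cannot be quantified from the article.

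The conclusion assumes that the sentence is applied literally and that the relatedness and communication steps are confined to SAEs, as the article states them. If the full protocol and the case report form already use outcome criteria, only the article's wording needs correction.

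**What to change.** Replace the sentence with an outcome-based definition. For example: an SAE is any untoward medical occurrence, whether or not related to the study, that results in death, is life-threatening, requires or prolongs hospitalisation, causes persistent or significant disability, or is otherwise medically important.

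Record severity as a separate grade for every AE, so that intensity and seriousness are never inferred from each other. Then confirm that the full protocol and the case report form carry the same definition. If events have already been recorded under the severity wording, check registered AEs against the outcome criteria before the half-way review.

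The cost is a wording change, possibly one extra field on the case report form, and slightly more events classed and reported as SAEs. The sample size and the primary analysis do not change.
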